### Measures

#### Diagnostic and baseline assessments

The Dutch DSM-5 versions of the Structured Clinical Interview for DSM-5 Disorders—SCID-5-S and SCID-5-P—were used to assess syndromal and personality disorders during screening (22, 36). A checklist is used to assess the inclusion and exclusion criteria. Furthermore, at baseline, the Childhood Trauma Questionnaire-Short Form [CTQ-SF; (37)], PCL-5, Young Schema Questionnaire-Short Form, Schema Mode Inventory, and (after preparatory session 3 with the individual therapist) WAI self-report questionnaire (38) were assessed.

Adverse childhood experiences are assessed by the Childhood Trauma Questionnaire-Short Form [CTQ-SF; (37)], a self-reported questionnaire comprising 25 items. These items are rated on a 5-point Likert scale, ranging from 1 (never true) to 5 (very often true). The CTQ-SF encompasses the following five subcategories: sexual abuse, physical abuse, emotional abuse, physical neglect, and emotional neglect. The CTQ-SF has demonstrated satisfactory validity and reliability, with Cronbach's alpha ranging from 0.53 (physical neglect) to 0.91 (sexual abuse) (39, 40). To assess the severity of trauma exposure, norm scores are available, categorizing individuals into four groups: none, low, moderate, and severe (41).

#### Primary outcome measures

The primary focus of the study is to determine changes in the severity and frequency of DSM-5 BPD manifestations, assessed with the Borderline Personality Disorder Severity Index version 5 (BPDSI-5) (42). The BPDSI-5 is a structured clinical interview that employs 70 items to assess the severity of BPD within the preceding 3 months. The items assess different manifestations of the nine BPD traits outlined in the DSM-5. Each of these nine traits is evaluated using multiple items. The frequency of occurrence indicated by each item is evaluated using an 11-point Likert scale, ranging from 0 (absent) to 10 (daily). However, the 'identity disturbance' trait diverges, utilizing a 5-point Likert scale from 0 (not present) to 4 (dominant), which is then multiplied by 2.5. For each BPD trait, a subscale score is calculated consisting of the mean of the pertinent items (range 0–10). The total score of the BPDSI-5 score ranges from 0 to 90, reflecting overall severity. The psychometric properties of the BPDSI-5 are good, with a high level of agreement between different raters and high internal consistency. The scale has a cutoff point of 14.93 with scores above, indicating clinical levels of BPD dysfunction and exhibiting considerable specificity (1.00) and sensitivity (0.97). Additionally, Giesen-Bloo et al. (42) concluded that a reliable positive change is indicated by an improvement of at least 11.70 points.

#### Secondary outcome measures

1. Treatment dropout. The number of sessions and the date on which treatment dropout (or pushout) occurred will be monitored.

2. The working alliance self-report (WAI-SR) is used to measure patients' thoughts and feelings about the working relationship with the individual ST therapist (38). The WAI-SR has three scales that measure different aspects of the therapeutic alliance. each aspect is measured by four items. The scales are (1) agreement on the tasks of therapy, (2) agreement on the goals of therapy, and (3) the development of an affective bond. the items are scored on a 5-point likert scale. the goal, task, and bond domains have scores ranging from 5 to 20. Higher scores indicate a better therapeutic alliance. the WAI-SR demonstrates strong internal consistency; values of cronbach's alpha for each of the three subscales range from 0.81 to 0.90, while the total score has cronbach's alpha of 0.91. the WAI-SR also exhibits considerable reliability, with a test–retest reliability of 0.93 (95% CI 0.83–0.97) (43). in terms of its construct validity, the WAI-SR exhibits high correlations with other measures of the therapeutic alliance, such as a correlation of 0.80 with the california psychotherapy alliance scale and a correlation of 0.74 with the helping alliance questionnaire (44). The first assessment of the WAI-SR took place 3 weeks after starting therapy, during the preparation phase, because some experience with the treatment and contact with the therapist is needed to answer the WAI questions. note that this is before the imrs sessions start in the experimental arm A. participants were instructed to fill out the WAI after this session and return it before the fourth individual session in a sealed envelope to the secretary (and not give it to the therapist) to prevent their ratings from being influenced by therapists reading their ratings. the later WAIs are part of the computerized battery that participants fill in during regular assessments, which are assessed by an independent research assistant.

3. The WHO disability assessment schedule 2.0 36-item interview version (WHODAS 2.0) (45) is used to assess general functioning, measuring impairment in six domains: cognition, mobility, self-care, getting along, life activities, and participation. In this study, the WHODAS is administered by the independent research assistant. All items are assessed using a 5-point likert scale, with scores ranging from 1 (non) to 5 (extreme or cannot do), based on the person's experience in the past 30 days. a summary score will be derived using the complex scoring method (45). The WHODAS 2.0 has excellent psychometric properties. Test–retest studies of the 36-item scale in countries across the world found it to be highly reliable, with an intraclass coefficient of 0.69–0.89 at the item level, 0.93– 0.96 at the domain level, and 0.98 at the overall level. cronbach's alpha levels were generally very high (0.94–0.96 for domains and 0.98 for total score) (45).

4. Early maladaptive schemas were assessed using the Dutch Young Schema Questionnaire-3 Short Form [YSQ-3SF; (46)]. In the current study, the sum score of the schemas from the disconnection/rejection domain is used to test the hypothesis that early ImRs leads to a faster reduction of schemas from this domain. The sum of the scores of the other domains is used for exploratory purposes. The YSQ-3SF consists of 90 items with a 6-point Likert scale ranging from 1 (completely untrue of me) to 6 (describes me perfectly) for measuring 18 schemas, as formulated by Young et al. (33). The psychometric properties of the YSQ-3SF are good, with a test–retest reliability of 0.98 and adequate internal consistency for all 18 scales (α > 0.70). In addition, a significant association has been found between the schemas measured by this questionnaire and features of several personality disorders (46, 47).

5. The severity of posttraumatic stress symptoms is measured using the Post-Traumatic Checklist for DSM-5 (PCL-5) (48). The PCL-5 is a self-report measure for PTSD symptoms with 20 items which are rated on a 5-point Likert scale, from 0 (not at all) to 4 (extremely), assessing the 20 DSM-5 symptoms of PTSD. The PCL-5 provides a severity score between 0 and 80, and the developers suggest that a PCL-5 cutoff score between 31 and 33 is indicative of probable PTSD. Although a diagnosis cannot be made on the basis of the PCL-5 alone, clinicians can look at individual items to determine whether the number of symptoms required by the DSM-5 is present. The PCL-5 has good psychometric properties with good internal consistency (α = 0.96), test–retest reliability (*r* = 0.84), and convergent and discriminant validity (49–51).

6. Quality of Life will be assessed with the EuroQol EQ-5D-5L (52, 53). Five dimensions (mobility, self-care, usual activities, pain/discomfort, and anxiety/depression) are measured and categorized into five severity levels: no problems, slight problems, moderate problems, severe problems, and extreme problems. There are 3,125 possible health states defined by combining one level from each dimension, ranging from 11,111 (full health) to 55,555 (worst health). EQ-5D-5L health states are converted into a single index ‘utility' score using a scoring algorithm based on (Dutch) public preferences. The EQ-5D-5L has good psychometric properties. The intraclass correlation of the EQ-5D-5L ranges from 0.73 to 0.84 for the summary index, and the instrument has good construct validity (54).

7. The SMI is a self-report instrument that consists of 143 items on 16 schema modes that are scored on six-point Likert scales (1 = *completely untrue*, 6 = *completely true)*. It measures the extent to which dysfunctional (vulnerable child, angry child, enraged child, impulsive child, undisciplined child compliant surrender, detached protector, self-soother, self-aggrandizer, bully and attack, punitive parent, demanding parent, healthy adult, perfectionistic overcontroller, and suspicious overcontroller) and functional schema modes (happy child and healthy adult) were present at the time of assessment (55). It is an adaptation of the original SMI containing 270 items (56) and a short SMI containing 118 items (57). Its subscales have satisfactory to high internal consistency (Cronbach's α ranges from 0.79 to 0.96) (57).

8. General psychopathological symptoms as an index of the severity of syndromal disorders are assessed with the Brief Symptom Inventory [BSI; (58)], a short version of the Symptom-Check-List (SCL-90-R). The BSI is a self-reporting instrument that measures general psychiatric symptoms. It measures nine symptom dimensions: somatization, obsession-compulsion, interpersonal sensitivity, depression, anxiety, hostility, phobic anxiety, paranoid ideation, and psychoticism with 53 items scored on a 5-point Likert scale, ranging from 0 (not at all) to 4 (extremely). The BSI has good reliability and validity. The internal consistency of the total score is 0.96, and the test–retest reliability is 0.90 (59). Normative data are available for both clinical and non-clinical samples of adolescents (over 13 years) and adults (60).

9. Happiness is assessed with the 1-item happiness question validated in more than 30 countries (61). General happiness, in the weeks prior to the assessment, is assessed by a single 7-point Likert scale item ranging from 1 (completely unhappy) to 7 (completely happy). The reliability and validity of the happiness item are good to excellent, with a test–retest reliability of 0.87 (62).

10. Medication and mental healthcare use are monitored during each assessment.

### Study assessment moments

Outcome instruments are assessed at baseline (0 months), at 4 months (12 sessions of ImRs or ST-as-Usual), after 8 months of treatment, after 1 year of treatment, at the end of group therapy (after 18 months of treatment), and after 24 months (after the end of individual treatment). One year later, a 3-year follow-up assessment is performed. Table 1 presents an overview of the measurements and the timeframe of the assessments.

The WAI, assessing the therapeutic alliance with the individual therapist as experienced by the participant, cannot be assessed at baseline because the patient and therapist have not yet met each other. Therefore, the first WAI assessment will take place after the third individual session, that is, before the ImRs in the experimental arm is started.

### Statistical analysis

All analyses are planned to be carried out using SPSS or R statistical software. Dimensional outcomes will be analyzed with multilevel analysis using all available data (intent-to-treat principle). Depending on the empirically found distribution of the dependent variable, the appropriate (generalized) linear mixed model will be chosen (e.g., in the case of non-normal distribution, gamma, negative binomial, or Tweedie distributions with a loglink). Time models might be linear, curvilinear, or piecewise, depending on which model fits the data best. The fixed part will contain the main effects of time and treatment arm and their interaction. The random part will contain a covariance structure for the repeated part with the best fit to the data (e.g., AR1, ARMA11, and compound symmetry) and a random intercept for group and/or participant and/or random slopes for time. Adding a random part for each group is important because of the interdependence of assessments of participants per GST group. If necessary, that is in case of substantial differences between treatment arms at baseline, differences at baseline will be controlled for by adding covariates to the model. Multiple imputation methods will be used to handle missing values at the item level. However, completely missing measurements will not be imputed as this is not necessary for multilevel analysis (63). Dropout will be analyzed using survival analysis, with the treatment arm as a factor. If data allow, a multilevel survival analysis will be used to take the dependency of observation by group into account (group as random intercept). The study will use (G)LMM analyses to test predictors and moderators, including working alliances, schema modes, and PTSD symptoms. The analysis will involve adding predictor, predictor x time, predictor x treatment, and predictor x time x treatment interactions to the model.

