## Method

### Design

This study design is a multicenter RCT, with two arms (*n* ≥ 73). Both treatments consist of a combination of individual and group sessions. There are two versions of individual ST, to which participants are randomly assigned: (A) experimental ST, in which ImRs is delivered in every individual session during months 2–4 (early ImRs), and (B) STAU, in which patients receive ST-as-Usual, that is, ImRs is not allowed during months 2–4. Therapists in this condition are allowed to use other ST (experiential) techniques, such as chair work and cognitive and behavioral techniques, but are not allowed to use ImRs. After 4 months, therapists are free to use all ST techniques that they think are appropriate and helpful. This study is being carried out in five corporate mental healthcare centers in the Netherlands: GGZ Oost Brabant (locations Helmond and Oss), and PsyQ locations Amsterdam, Rotterdam, and Zaandam. During the study, the PsyQ location in Amsterdam was taken over by the Academic Center for Trauma and Personality (ACTP).

In two PsyQ sites (Amsterdam and Rotterdam), several participants also took part in the Borderline Optimal Treatment Selection (BOOTS) study. The BOOTS study compares the effectiveness of DBT to ST and investigates the optimal treatment selection among individuals with BPD (21). Eighteen participants participated in the BOOTS trial and were randomized to the ST arm. They completed the assessments needed for the BOOTS and the LUCY trial, after which they were randomized to one of the two arms of the LUCY trial.

The study protocol was approved by the ethical committee of the University of Amsterdam (2019-CP-10845). This study is registered at the International Clinical Trial Registry Platform, registration number NL NL7965, first registered on 15 August 2019 and fulfills the World Health Organization Trial Registration Data Set. The procedures adhered to applicable guidelines and regulations. Any changes in the protocol will undergo formal amendments. The ethical committee of the University of Amsterdam will review the amendments, and, upon approval, they will be included in the trial registration.

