### Randomization

When participants were eligible for participation and completed baseline assessments, they were randomized to one of the two arms A (early ImRs) or B (STAU) in a 1:1 proportion by an independent researcher, after checking the inclusion and exclusion criteria, using block randomization with randomized block sizes blocks (sizes 4 and 6), stratified by the center (for the Amsterdam site stratified for language) (29, 30). The allocated treatment condition was disclosed to the patient by their therapist during the first treatment session.

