One site delivers intensive day clinical treatment. The treatment duration at this site is 24 months, divided into four phases; phase 1 has a duration of 6 months in which group ST is given three times a week for 90 min plus one individual session with a duration of 45 min. In phase 2, months 7–12: group ST is delivered 2 times a week for 90 min, accompanied by one individual session every 2 weeks, for 45 min. In phase 3, months 13–18, GST is delivered once a week for 90 min, and individual sessions are delivered once every 2 weeks for 3 months and thereafter once a month. In phase 4, one group therapy session is provided every 2 weeks, and individual sessions once every 2 months.

Group ST follows the protocol of Farrell et al. (34) and individual ST the protocol of Arntz and van Genderen (9). Group and individual ST are coordinated during weekly peer supervision meetings. The groups are semi-closed: every 12 sessions, patients can be included until the group is complete, participants who complete 1.5 years of treatment leave the group, and in the following session, new patients enter the group.

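### The stratified randomization is not carried into the stated mixed model: no center or language term, and the therapy-group intercept is optional; the error is small and conservative

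*Protocol article*

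**What the plan says.** **Design.** The Randomization section allocates eligible patients to "one of the two arms A (early ImRs) or B (STAU) in a 1:1 proportion by an independent researcher", in blocks of 4 and 6, "stratified by the center (for the Amsterdam site stratified for language"). The Design section says "This study is being carried out in five corporate mental healthcare centers in the Netherlands" and lists Helmond, Oss, Amsterdam, Rotterdam and Zaandam. Counting each location as a center and splitting Amsterdam by language gives six strata.

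**Model.** The Statistical analysis section states: "The fixed part will contain the main effects of time and treatment arm and their interaction". The random part may hold "a random intercept for group and/or participant and/or random slopes for time". The section adds: "Adding a random part for each group is important because of the interdependence of assessments of participants per GST group". Other covariates enter only "in case of substantial differences between treatment arms at baseline, differences at baseline will be controlled for by adding covariates to the model". Dropout is analyzed by survival methods with arm as the factor, and with a group effect if the data permit. Neither center nor language is named in any of these models.

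**Sites.** The Treatment section says "One site delivers intensive day clinical treatment", with group sessions three times a week in the first six months and a four-phase, 24-month course. Elsewhere group sessions are weekly and end at 18 months.

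**Power.** The Sample size section bases its more refined calculation on a difference in linear slopes over seven measurements, two-sided at 0.05.

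**The concern.** Blocking within strata keeps the arms balanced on center and language. If the strata differ in outcome and the model ignores them, that between-stratum variance stays in the error term. The standard error of the arm contrast is then larger than the true sampling variability, and the test is conservative.

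The routes by which the strata might enter the model are weak. The baseline-difference rule will seldom bring them in, because blocking keeps the arms alike on exactly these factors. The therapy-group intercept would carry most level differences if groups sit within one site and language, but the and/or wording does not require it. An intercept also does not capture different trajectories over time. Such trajectories are plausible here: the day-clinic site follows another schedule, and the article itself plans to explore whether that dosage difference affects outcome.

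At stake are some precision and a clear prespecification. With no stratum term named, adjusting for site becomes a choice made after the data are seen.

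**Working it through.** **1. The plan's own figures.** The repeated-measures approximation is n per arm = 2(z₀.₉₇₅ + z₀.₈₀)²[1 + (T−1)ρ]/(T d²). With T = 7, ρ = 0.5 and d = 0.5 this is 2 × 7.849 × 4/(7 × 0.25) = 35.9, so 36 per arm and N = 72. At N = 73 the power is 80.7%. The stated 73 is reproduced. Scaling the stated slope result (N = 39 for 80%) to N = 66 gives 95.4% power at d = 0.5, and a detectable effect of 0.5 × √(39/66) = 0.384 at 80%. This agrees with the article's figures of more than 95% and 0.38.

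**2. Slope test, strata differing in level only.** A constant stratum shift adds the same amount to every visit of a participant and cancels from that participant's slope. Simulations used 72 patients, six strata, seven visits, 1:1 allocation within stratum and 6,000 runs per scenario. The slope standard error was 0.2292 without and with strata at a stratum share of 0.10 of the intercept variance, and 0.2293 without and with at 0.20. Direct mixed-model fits gave a ratio of 1.000.

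**3. Slope test, strata differing in trajectory.** The documents give no size, so the following are assumptions. Scale months 0, 4, 8, 12, 18, 24 and 36 by 36; the sum of squares about the mean is 0.720. With total variance 1 and correlation 0.5, the residual variance is 0.5. The variance of a participant's fitted slope is then 0.5/0.720 = 0.694, or 0.944 if a random-slope SD of 0.5 is added.

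- *All six strata vary in slope* (5% to 10% of the random-slope variance): the simulated standard error falls from 0.2285 to 0.2272, and from 0.2289 to 0.2262, when stratum-by-time is fitted. Without it the standard error is overstated by about 0.6% to 1.2%.
- *Only the day-clinic site diverges*, with 20% of patients (one center in five) and a linear divergence of δ SD by month 36. The omitted variance is 0.2 × 0.8 × δ² = 0.16δ², and the ratio of standard errors is √(1 + 0.16δ²/V).

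| δ | V = 0.694 | V = 0.944 |
|---|---|---|
| 0.25 | 1.007 | 1.005 |
| 0.5 | 1.028 | 1.021 |
| 1.0 | 1.109 | 1.081 |

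A δ of 0.5 is about the five BPDSI points that the Sample size section calls relevant. Its true type I error is 2Φ(−1.96 × 1.028) = 4.4% against a nominal 5%.

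**4. Time-averaged contrast, no group term.** Take an intercept variance of 0.5, a residual variance of 0.5 over seven visits, and the same random slope. The variance of a participant mean is 0.5 + 0.5/7 + 0.25 × 0.405² = 0.612. With stratum variance τ² inside that total and six strata of 12, the ratio is √[1 + τ²(60/70)/(0.612 − τ²)].

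| Share of intercept variance | τ² | Ratio by formula | Simulated standard errors, without/with strata | Simulated type I error, strata omitted |
|---|---|---|---|---|
| 0.05 | 0.025 | 1.018 | 0.1836/0.1804 | 4.7% |
| 0.10 | 0.05 | 1.037 | 0.1831/0.1765 | 4.3% |
| 0.20 | 0.10 | 1.080 | 0.1823/0.1688 | 3.5% |

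**5. What the group intercept recovers.** The simulation placed 12 groups of six within the six strata, both arms in each group, with stratum variance 0.1 and participant variance 0.4. The standard error of the arm term was 0.193 with neither term, 0.181 with a group intercept and 0.181 with strata. The standard error of time-by-arm was 0.194 in all three.

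**The case against.** The strongest reply has four parts.

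- **The model has a random part.** It is not limited to the three fixed effects, and the article itself calls the group term important. If groups sit within site and language (the English-speaking cohort formed one group), a group intercept recovers nearly all of the level loss, as step 5 shows. This stands, but only if the term is fitted, and it does not address differing trajectories.
- **The powered test is a slope test.** Constant stratum shifts cancel from it. This stands for a linear model. With a log link or a non-linear time model, both of which the section allows, the cancellation need not be exact; that case is not quantified here.
- **The error is conservative.** This also stands. A reader might infer that valid inference requires the strata, or that stratifying achieved nothing. Neither follows: type I error is not inflated, and blocking still balances the arms within center and language. A reader might also infer that power drops below the planned 80%. The Sample size section mentions no stratum adjustment in that figure, so leaving the strata out does not take power below plan; adjusting would add a little.
- **This is a condensed article, and a fuller analysis plan may name the strata.** That is possible. But the article does more than stay silent: it lists the fixed effects and gives a covariate rule that would hardly ever admit the strata.

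**Conclusion.** The point holds as a mismatch between design and stated model, with a small and conservative effect.

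- **Primary linear slope test:** no effect from omitting stratum main effects. About 1% to 3% overstatement of the standard error if trajectories differ as assumed, and more (about 8% to 11%) only if the day-clinic site diverges by as much as 1 SD.
- **Time-averaged or level contrasts without a group term:** about 2% to 4% overstatement if strata explain 5% to 10% of participant-level variance. A therapy-group intercept largely removes it.

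These sizes rest on assumed stratum shares, an assumed 20% of patients at the day-clinic site and an assumed linear divergence. The documents supply none of them. The case for acting is that the change costs little and settles the site terms in advance.

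**What to change.** State in the analysis plan, before outcome data are analyzed by arm:

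1. The six-level randomization stratum (center, with Amsterdam split by language) is a fixed effect in the primary and secondary mixed models.
2. At least a day-clinic-site-by-time term is included, using the same time function as the arm comparison.
3. The therapy-group random intercept is mandatory, with a named fallback if the model does not converge.

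Cost: about five degrees of freedom for the stratum main effect, counted against roughly 66 to 73 participants because strata vary between participants. Site-by-time takes one more with linear time, and more if time is curvilinear or piecewise. Full stratum-by-time would cost five or more and is not needed for the main purpose.

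Stratifying the dropout analysis is optional. With 73/6 ≈ 12 patients per stratum and the article's 20% first-year dropout, each stratum would have about 12 × 0.20 = 2.4 events in that year.

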### Sample size

At least *N* = 73 participants were planned to be included. Using the approximation proposed by Twisk (25), and assuming an average correlation of 0.5 between measurements [as in (26)], this suffices, given the seven repeated measurements, to reach 80% power to detect a medium effect size of *d* = 0.5 between the treatment conditions. Using the more sophisticated power analysis approach proposed by Moerbeek et al. [(27), p. 191] for multilevel tests of a difference in linear slopes assessed with multiple (i.e., 7) measurements, for a medium effect size (*d* = 0.5) tested at a two-tailed significance level of 0.05, *N* = 39 suffices to reach 80% power. Starting with *N* = 73 and taking into account an early study dropout of 10%, the resulting N=66 suffices to reach > 95% power to detect a medium effect size (*d* = 0.5) and 80% power to detect a small-to-medium effect size of *d* = 0.38. An effect size of *d* = 0.5 between slopes is equivalent to a mean difference between conditions of approximately five points on the BPDSI at the last assessment, which is a relevant difference. Moreover, the sample size of N = 73 suffices to reach more than 80% power to detect at a significance level of 0.05, a difference of 30% in dropout rates during the first year between 20% [which is the approximate dropout rate of ST in individual-group format at 1 year; (26)] and 50%, which would be a substantial and alarming increase in the experimental treatment (25, 28).

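### Baseline adjustment depends on an undefined look at imbalance while the model leaves the arms free to differ at a pre-randomization baseline: valid, but less precise and data-dependent

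*Protocol article*

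**What the plan says.** Three statements in the protocol article bear on this.

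- **Model (Statistical analysis).** "The fixed part will contain the main effects of time and treatment arm and their interaction". The time trend may be linear, curvilinear or piecewise, and the distribution, covariance structure and random effects are chosen by fit.
- **Adjustment rule (Statistical analysis).** Adjustment is conditional: "in case of substantial differences between treatment arms at baseline, differences at baseline will be controlled for by adding covariates to the model". No threshold is given and no covariates are named.
- **Timing of baseline (Randomization; also Procedure and assessments).** "When participants were eligible for participation and completed baseline assessments, they were randomized to one of the two arms", in a 1:1 ratio.

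Table 1 lists the BPDSI at baseline and at 4, 8, 12, 18, 24 and 36 months. These are the seven repeated measurements on which the Sample size section relies, so baseline BPDSI is part of the outcome vector.

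**The concern.** Because baseline precedes randomization, the expected arm difference at month 0 is zero and any observed difference is due to chance. The planned model estimates that difference all the same, through the arm main effect. The arm-by-time term then compares change from baseline, and the information that the arms start from the same population mean goes unused.

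The adjustment rule is a second, separate matter. How much a covariate helps depends on how strongly it predicts outcome, not on whether the arms happen to differ on it. A rule triggered by observed imbalance gives up precision when the arms look alike. When they do not, it makes the fitted model depend on the data. With no threshold and no covariate list, the analyst can choose between an adjusted and an unadjusted treatment estimate after seeing the data. This comes on top of the choices of time shape, distribution and covariance already left to fit, in a trial of 66 to 73 patients.

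**Working it through.** **Inputs from the document.** Sample size: N = 73, or 66 after 10% early study dropout; "assuming an average correlation of 0.5 between measurements"; seven measurements; d = 0.5, described as "equivalent to a mean difference between conditions of approximately five points on the BPDSI at the last assessment"; "tested at a two-tailed significance level of 0.05". Allocation is 1:1, so 33 per arm at N = 66. Visits are at months 0, 4, 8, 12, 18, 24 and 36.

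**Assumptions.** SD about 10 (5 points / 0.5); compound symmetry, because the document gives only an average correlation; complete data on the 66.

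**1. The plan's own figure.** Under the simpler repeated-measures approximation, N = 73 "this suffices, given the seven repeated measurements, to reach 80% power to detect a medium effect size of" d = 0.5. Total N = 2 × 2(1.960 + 0.842)²[1 + (T−1)ρ]/(T d²). With ρ = 0.5 this gives 71.8 for T = 7 and 73.3 for T = 6 (follow-ups only), so 73 reproduces to within two patients. The slope-based figure of N = 39 was not reproduced, because the standardisation behind it is not given. The powers below therefore compare two analyses on the same assumptions. They do not re-audit the stated power.

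**2. Slope difference, free against common baseline mean.** Let A = X′V⁻¹X for one patient, with an intercept and time in X and unit SD. With n per arm:

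- free arm difference at baseline: Var = 2 / [n(A₂₂ − A₁₂²/A₁₁)]
- common baseline mean: Var = 2 / (n A₂₂)

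Here Σt = 102 and Σt² = 2420. Under compound symmetry with ρ = 0.5, V⁻¹ = 2(I − 0.125J), so:

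- A₁₁ = 2(7 − 0.125 × 49) = 1.75
- A₁₂ = 2(102 − 0.125 × 7 × 102) = 25.5
- A₂₂ = 2(2420 − 0.125 × 102²) = 2239
- A₁₂²/A₁₁ = 371.6

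The variance cut is 371.6/2239 = 16.6%. Scaled to points at month 36 (multiply by 36 × 10, n = 33):

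| Model | SE | Power for 5 points |
|---|---|---|
| Free arm difference at baseline | 360 × √(0.001071/33) = 2.05 | 68% |
| Common baseline mean | 360 × √(0.000893/33) = 1.87 | 76% |

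**3. Sensitivity of the slope gain.**

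- Compound symmetry, ρ from 0.3 to 0.7: about 28% down to 8%.
- Random slopes added at ρ = 0.5, with slope SD of 0.3 to 1.0 baseline SDs over 36 months: about 15% down to 7%. Other assumed values went as low as about 4%.
- AR1 by visit with lag-one correlation 0.8 or 0.7 (average correlation 0.58 or 0.44): about 31% or 40%.

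**4. Other contrasts at ρ = 0.5.** For the mean of m follow-up visits, the change-score variance is [1+(m−1)ρ]/m + 1 − 2ρ, and the baseline-adjusted variance is [1+(m−1)ρ]/m − ρ².

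- One visit: 1.00 to 0.75 (−25%).
- Mean of three visits: 0.667 to 0.417 (−37.5%); SE 2.01 to 1.59, power 70% to 88%.

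**The case against.** The strongest reply is that time, arm and arm-by-time with baseline among the outcomes is a standard, valid longitudinal model for a randomized trial. That stands: a chance BPDSI difference at baseline is absorbed by the arm main effect, and the planned contrast is not biased by it. A reader might infer bias from the free baseline mean, but the documents do not support that; the loss is one of efficiency.

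A reader might also quote a gain of 25% to 38%, or power rising from 70% to 88%. Those figures belong to a single visit and to a three-visit mean. The slope-based power calculation in the Sample size section concerns a difference in linear slopes over seven measurements, where the cut is about 17% under compound symmetry. It is smaller with random slopes and larger under AR1, so no single figure holds without its conditions.

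Nor does the document say that baseline BPDSI would be entered as a covariate while it remains an outcome. The rule may be meant for other characteristics, so a charge of using baseline twice has no support in the text.

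Finally, the article condenses a fuller plan, and a threshold and covariate list may sit there. Their absence is therefore not the point. The imbalance trigger itself is stated here, and it remains open to criticism even with a defined threshold.

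**Conclusion.** The point holds as one of efficiency and pre-specification. The imbalance trigger is the weaker part of the plan, because it lets the data decide which treatment estimate is reported. The free baseline mean is a missed gain in a valid model.

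For the linear slope, the gain is about 17% of the variance, or 8 percentage points of power at N = 66. This rests on an SD of about 10, compound symmetry, a correlation of 0.5 and a 5-point difference at month 36. The direction of the gain is the same in every linear covariance structure tried, but its size is not. None of the figures carries over exactly to the log-link models that the Statistical analysis section also allows.

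**What to change.** Delete the rule that ties adjustment to observed imbalance. For BPDSI-5, and for each secondary outcome with a pre-randomization baseline, pre-specify a model in which both arms share one mean at month 0 and arm effects enter only after baseline. With a linear trend this means time and arm-by-time without an arm main effect, with time coded zero at baseline. Leave the WAI-SR out: it is first taken after the third individual session, so randomization does not guarantee equal means there.

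The alternative is to take baseline out of the outcome vector and always include it as a covariate. The common-mean model is preferable because it keeps patients without follow-up in the likelihood, in line with the plan's intention to use all available data. Any other covariates should be named in advance for their expected link with outcome.

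The cost is analysis wording, settled before outcomes are compared by arm. The constraint saves one parameter, whereas each covariate uses one degree of freedom. Recruitment, treatment and assessments are unaffected.
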